**Pharmacological interaction between duloxetine and**

**3,4-Methylenedioxymethamphetamine (MDMA, Ecstasy)**

# SYNOPSIS

| Sponsor | Clinical Pharmacology & Toxicology, University Hospital Basel |
| --- | --- |
| Study title | Pharmacological interaction between duloxetine and 3,4-Methylenedioxy­­methamphetamine (MDMA, “Ecstasy”) |
|  |  |
| Study site | Divisions of Clinical Pharmacology & Toxicology, University Hospital Basel |
| Objectives | **Primary study endpoints**   1. Effect of duloxetine on the subjective response to MDMA   **Secondary study endpoints**   1. Effect of duloxetine on physiological responses to MDMA 2. Tolerability of MDMA and duloxetine 3. Effect of duloxetine on neuroendocrine effects of MDMA 4. Effects of duloxetine on pharmacokinetics of MDMA 5. Effect of MDMA on duloxetine pharmacokinetics |
| Design | Randomized, placebo-controlled, cross-over study |
| Analytics | Determination of plasma concentrations of MDMA, metabolites and duloxetine by GC-MS/LC-MS/MS |
| Subjects | 16 healthy volunteers (men or women), age: 19-45 years |
| Drugs | Duloxetine (Cymbalta®) and MDMA (3,4-methylene­­dioxy­­meth­­amphetamine) |
| Study dates | Start: 1.1.2010, End: 31.12.2010 |

# Abbreviations and Definitions

ASAT aspartate transferase

ALAT alanine aminotransferase

AE adverse event

ANOVA analysis of variance

AMRS adjective mood rating scale

ARCI addiction research center inventory

AUC area under the concentration time curve

BAG Bundesamt für Gesundheitswesen = Swiss Federal Office of Public Health

BP blood pressure

CHF Swiss francs

CRF case report form

CRTT choice reaction time test

CRC clinical research center

CRP C-reactive proteine

CYP cytochrome P450 enzyme

Cmax maximum concentration

Cl chloride

Ca calcium

5D-ASC 5 dimensions of altered states of consciousness

EWL Eigenschaftswörterliste = AMRS

Ecstasy may contain MDMA or other substances at various amounts

EKBB Ethische Kommission beider Basel

ECG electrocardigram

EOS end of study

GCP good clinical practice

GC-MS gas chromatography-mass spectrometry

GMP good manufacturing practice

-GT gamma-glutamyl transferase

HPLC high-pressure liquid chromatography

5-HT serotonin

HR heart rate

HMA 4-hydroxy-3-methoxyamphetamine

HMMA 4-hydroxy-3-mehoxymethamphetamine

5-HIAA 5-hydroxy indole acetic acid

IRB institutional ethics board = EKBB

K potassium

LSD lysergic acid diethylamine

LC list of complaints

LDH laccate dehydrogenase

LC-MS liquid chromatography-mass spectroscopy

MDMA 3,4-Methylenedioxymethamphetamine

MDA 3,4-methylenedioxyamphetamine

MD medical doctor

NE norepinephrine = noradrenaline

Na sodium

P phosphorus

PK pharmacokinetic

PI principal investigator

Psys systolic blood pressure

PhD Philosophical doctor ([name]. II)

THC tetrahydrocannabinol

SAE serious adverse event

SSRI selective serotonin uptake inhibitor

STAI state-trait anxiety inventory

SD standard deviation

T1/2 Plasma eliminiation half-life

Tmax time to reach Cmax

VAS visual analogue scale

# SUMMARY

3,4-methylenedioxymethamphetamine (MDMA, “ecstasy”) is widely used by young people for its euphoric effects. MDMA releases serotonin (5-HT), norepinephrine (NE), and dopamine through an interaction with the corresponding presynaptic monoamine uptake transporter. 5-HT transport inhibitors block MDMA-induced 5-HT release in vitro or in animals and also attenuate the subjective and cardiovascular response to MDMA in humans. NE transport inhibitors similarly prevent the MDMA-induced release of NE in cell assays and attenuate behavioral effects of MDMA in animals. Effects of the NE transporter inhibitor reboxetine on the response to MDMA in humans are currently investigated. Here we suggest evaluating effects of pretreatment with the combined 5-HT and NE transport blocker duloxetine on the pharmacodynamics and pharmacokinetics of MDMA. The study will use a randomized double-blind cross-over design with four experimental sessions. Duloxetine (120 mg) or placebo will be administered 16 h and 4 h before the administration of MDMA (125 mg) or placebo to 16 healthy volunteers. Subjective and cardiovascular responses and plasma samples for pharmacokinetics will be repeatedly assessed throughout the experiments. We hypothesize that duloxetine will attenuate the subjective and cardiovascular response to MDMA.

**Key words:** MDMA, 3,4-Methylenedioxymethamphetamine, Ecstasy, norepinephrine, reboxetine, pharmacokinetics

# INTRODUCTION

3,4-methylenedioxymethamphetamine (MDMA, “ecstasy”) is widely used by young people for its euphoric effects. MDMA acts at the presynaptic monoamine transporter and releases serotonin (5-HT), dopamine (DA), and norepinephrine (NE) by reversing the transport of these monoamines. While the neurochemical effects of MDMA have been well studied in preclinical models, it is less clear how the neurochemistry translates into to the psychotropic and physiological effects in humans. Here, we suggest evaluating the functional role of 5-HT and NE in the pharmacology of MDMA in humans. We plan to test the effects of pretreatment with the selective and potent dual NE and 5-HT transport inhibitor duloxetine on the pharmacodynamics and pharmacokinetics of MDMA in healthy human volunteers. We hypothesize that duloxetine will attenuate subjective and cardiovascular responses to MDMA. Such a result would indicate that 5-HT and NE are critically involved in the pharmacology of MDMA and may provide helpful in the use and development of treatments for Ecstasy intoxications. The study shall take place in the Clinical Research Centre (CRC) of the Clinical Pharmacology Unit of the University Hospital of Basel.

# SIGNIFICANCE

Use of stimulant drugs including Ecstasy is highly prevalent in our society. In Switzerland, 2.2% of 15-39 year olds reported having used Ecstasy at least once [1]. Besides from being abused as a recreational drug, MDMA, the active substance usually found in Ecstasy pills, is being evaluated as a treatment for post-traumatic stress disorder in several countries including Switzerland. MDMA has also been suggested to be useful to treat and study mood disorders due to its potential to increase empathy and rapidly elevate mood [2, 3]. Ecstasy use can result in adverse and potentially fatal medical complications [4, 5]. Serious toxicity due to Ecstasy use is relatively rare but may be seen in up to ten percent of patients presenting to Emergency Departments with medical problems due to Ecstasy use [4]. Extensive Ecstasy use has also been associated with neurotoxic effects to serotonergic brain neurons [6]. Because MDMA is widely used, a better understanding of its pharmacology and toxicology is warranted.

# BACKGROUND

## Pharmacology of MDMA

In animals, MDMA releases presynaptic 5-HT, NE and to a lesser extent DA [7-9]. The MDMA-induced release of these monoamines is thought to be due to reverse-transport of monoamines through the corresponding uptake transporter. By blocking the interaction of MDMA with the 5-HT uptake site, 5-HT uptake inhibitors (SSRIs) decrease 5-HT release [9, 10] and the behavioral response to MDMA in animals [11, 12]. In humans, SSRIs including citalopram [13-15], fluoxetine [16], and paroxetine [17] similarly attenuated the subjective effects of MDMA. These findings confirm that the interaction of MDMA with the 5-HT uptake site is an important mode of action of this drug of abuse. However, blockade of MDMA-induced 5-HT release or postsynaptic antagonism of serotonin or dopamine receptors only partly blocked MDMA’s effects and other neurotransmitter systems are likely to contribute to the pharmacological response to MDMA [18]. In particular, recent evidence from in vitro and animal studies indicates an important role for NE in the pharmacology of MDMA. MDMA exhibits higher affinity for the NE transporter compared to the human 5-HT or DA uptake site [8, 19]. In addition, MDMA was more potent in releasing NE than 5-HT or DA from monoamine preloaded human embryonic kidney cells transfected with the corresponding human monoamine transporters [19]. The NE uptake transporter inhibitor desipramine reversed acute cognitive effects of MDMA in resus monkeys [20]. Further, doses of stimulants, which produce amphetamine-type subjective effects in humans, correlated with their potency to release NE and not DA release [8]. NE also plays an important role in mediating peripheral effects of MDMA. MDMA dramatically increases circulating plasma levels of NE [21]. The postsynaptic adrenergic 1 receptor antagonist prazosin reversed MDMA-associated locomotor stimulation in rats [22]. In addition, blockade of the effects of NE at postsynaptic 1 and 1-3 receptors reversed the hyperthermic response to MDMA in rats [21]. Further, blockade of the NE transporter abolished contraction of the rat aorta produced by 4-methylthioampethamine [23], a compound with a similar pharmacology to MDMA. Clinically, MDMA stimulates the sympathetic nervous system and increases heart rate, blood pressure and body temperature in controlled settings [15, 24]. Serious adverse effects of uncontrolled Ecstasy use also include hypertensive and hyperthermic reactions that are likely to be mediated by an activation of the adrenergic system by MDMA [5]. Together, the preclinical and clinical findings suggest that 5-HT and NE mediate most of the psychotropic and cardiovascular effects of MDMA in humans.

## Expected interactive effects of duloxetine and MDMA

### Pharmacodynamic interactions

Duloxetine (Cymbalta) is a potent inhibitor of the 5-HT and NE transporter [25-27]. In radioligand binding assays utilizing rat cortex synaptosomes, duloxetine possesses high affinity for both the NE and 5-HT transporter with Ki values of 2.1 and 0.53 nM, respectively [27]. Duloxetine is selective for the NE and 5-HT system and does not directly modulate the DA system. The affinity of duloxetine for the 5-HT transporter is similar to that of citalopram for this transporter (1.8 nM). We have previously shown that citalopram pretreatment significantly reduced the psychological and cardiovascular response to MDMA in healthy subjects [13, 15]. Because duloxetine is at least equally potent in blocking the 5-HT transporter compare to citalopram and also blocks the NE transporter with high potency we expect that duloxetine will be at least equally effective in decreasing the response to MDMA as citalopram. Actually, we hypothesize that duloxetine will be considerably more effective in reducing the cardiovascular effects of MDMA due to its additional binding to the NE transporter which is expected to prevent MDMA from interacting with the NE transporter to release NE [19]. The 5-HT and NE transport inhibition by duloxetine results in slight increases in brain 5-HT and NE [26]. In the present study, however, the ability of duloxetine to bind to the NE and 5-HT transporter is used to block the effects of MDMA which releases 5-HT and NE through an interaction with the NE and 5-HT transporter [8]. In preclinical studies, duloxetine prevented effects of different amphetamine derivatives with structural similarity to MDMA [26]. For example, duloxetine was shown to antagonize depletion of brain 5-HT by p-chloroamphetamine or of brain or heart NE by 6-HO-dopamine [26, 28]. No preclinical studies have studied the interaction of duloxetine and MDMA at the level of the NE or 5-HT transporter. Also no previous clinical study has addressed whether dual blockade of NE and 5-HT transport effectively blocks effects of stimulant drugs in humans. However, several compounds that block either 5-HT or NE transport have consistently been shown to block MDMA-induced release of NE or 5-HT in various assays [7, 8, 20, 29]. As noted above, 5-HT blockade reduced responses to MDMA in humans. Further, NE transport blockade with desipramine decreased acute cognitive effects of MDMA in resus monkeys [20]. In addition, recent clinical studies found that the NE transport blocker atomoxetine attenuated cocaine-induced systolic blood pressure increases [30] and cardiovascular and subjective responses to d-amphetamine [31]. These clinical data indicate that pretreatment with an NE transport antagonist decreases the cardiovascular stimulant effects of cocaine or d-amphetamine that have a very similar pharmacological action to MDMA. Together the data indicate that duloxetine will decrease the response to MDMA in healthy subjects.

### Pharmacokinetic interactions

Duloxetine is a substrate and inhibitor of CYP 2D6 [32] similar to MDMA [33]. Duloxetine may therefore increase MDMA plasma levels and vice versa. However, because MDMA itself inhibits CYP 2D6 (autoinhibition) the additive effect of duloxetine is expected to be small. Pretreatment with paroxetine which is considerably more potent in inhibiting CYP 2D6 than duloxetine increased MDMA plasma levels by only 30% [17]. Thus, we do not expect a relevant increase in MDMA Cmax or AUC when duloxetine is administered before MDMA (<30% increase in Cmax or AUC). On the other hand, MDMA may moderately increase Cmax and AUC of duloxetine thereby enhancing the pharmacodynamic interaction. This potential effect is not unwanted on the test day. However, we want to eliminate any carry-over effect from MDMA to the next test session to avoid elevated duloxetine levels due to MDMA-induced 2D6 inhibition. Therefore, test sessions will be separated by at least 10 days [33] to eliminate potential carry-over effects between sessions. The effect of CYP 2D6 inhibition on the PK of duloxetine has previously been studied and is moderate. Specifically, the maximum plasma concentration of duloxetine and the AUC increased 1.6-fold after pretreatment with the potent CYP 2D6 inhibitor paroxetine [32]. This moderate effect of 2D6 inhibition on the metabolism of duloxetine is explained by the fact that duloxetine is mainly metabolised by CYP 1A2 and only to a minor degree by CYP 2D6 [34].

# STUDY OBJECTIVES

We aim to test the effect of pretreatment with duloxetine on the subjective and cardiovascular effects of MDMA and on the pharmacokinetics of MDMA in humans.

## Primary study endpoints

1. Effect of duloxetine on the subjective response to MDMA

## Secondary study endpoints

1. Effect of duloxetine on cardiovascular effects of MDMA
2. Effect of duloxetine on pharmacokinetics of MDMA
3. Effect of MDMA on duloxetine pharmacokinetics
4. Tolerability of MDMA and duloxetine
5. Effect of duloxetine on neuroendocrine responses to MDMA

# HYPOTHESES

## Primary Hypotheses

1. Duloxetine will attenuate positive mood effects of MDMA. Specifically, co-administration of duloxetine with MDMA will result in a relative decrease in “good drug effects” VAS scores by 20% compared to the MDMA alone condition.

## Secondary Hypotheses

1. Duloxetine will reduce blood pressure and heart-rate increases produced by MDMA.
2. Duloxetine will increase Cmax and AUC0-6h of MDMA by <30%
3. MDMA will increase Cmax and AUC0-6h of duloxetine by <30%
4. MDMA and duloxetine will produce no severe adverse effects
5. Duloxetine will decrease neuroendocrine effects of MDMA

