#### Metabolism and Pharmacokinetics

After a single dose of MDMA tmax is attained at 120-144 min [44, 70]. T1/2 of MDMA (100 -125 mg dose) is about 8-9 h [71]. MDMA inhibits its own metabolism possibly by forming an enzyme-metabolite complex with CYP2D6. This autoinhibition likely explains the suggested non-linear pharmacokinetics of MDMA [33, 70-72]. There are two main metabolic pathways for the metabolism of MDMA [71]. MDMA is N-demethylated to 3,4-methlyenedioxyamphetamine (MDA). MDA is an active, but minor metabolite. CYP2D6-mediated O-demethylenation followed by COMT-catalyzed methylation leads to 4-hydroxy-3-mehoxymethamphetamine (HMMA) or 4-hydroxy-3-methoxyamphetamine (HMA). HMMA is the main metabolite of MDMA [71]. HMMA and HMA are rapidly glucuronidated or sulphate-conjugated.

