# Analytics

## MDMA and metabolites

MDMA, its active metabolite MDA and the main inactive metabolites HMMA and HMA will be determined in plasma by gas chromatography-mass spectrometry (GC-MS) by established techniques as previously described [77, 44, 78].

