## Analysis of outcomes

Repeated-measures analysis of variance (ANOVA) with drug (MDMA and duloxetine) as within-subject factors followed by Tukey’s post-hoc tests will be use to analyze differences between the different treatment conditions. Transformations will be performed before analysis, if response variables are nonnormally distributed. Pharmacokinetic parameters (Cmax, tmax, AUC from 0 to 6 h) will be obtained using *PK Functions for Excel*®. AUC values will be calculated by the trapezoidal rule. Additional PK analyses may be performed using *WinNonLin®* and *GraphPad®.* Statistical analyses will be performed using *Statistica*® *(StatSoft).*

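### The PK hypotheses claim increases below 30%, but the only test the protocol names is for a difference, which can neither support nor refute that bound

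*Protocol*

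**What the plan says.** Section 9.2 of the protocol states two bounded PK hypotheses: "Duloxetine will increase Cmax and AUC0-6h of MDMA by <30" percent, and "MDMA will increase Cmax and AUC0-6h of duloxetine by <30" percent. Section 7.2.2 gives the bound its meaning for MDMA: "we do not expect a relevant increase in MDMA Cmax or AUC when duloxetine is administered before MDMA (<30% increase in Cmax or AUC". There, AUC carries no time limit.

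Section 13.2 lists the PK measures ("Pharmacokinetic parameters (Cmax, tmax, AUC from 0 to 6 h) will be obtained") and names one inferential method: "Repeated-measures analysis of variance (ANOVA) with drug (MDMA and duloxetine) as within-subject factors followed by Tukey’s post-hoc tests will be use to analyze" differences between conditions. It mentions no ratio, confidence interval or comparison with 1.30. Section 13.1 gives no variance, margin or power for PK.

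Under section 10.1, two of the four conditions contain MDMA and two contain duloxetine. PK sampling ends 6 h after MDMA (section 11.4.5). Section 11.5.2.2 puts MDMA tmax at 120-144 min and says of the half-life: "100 -125 mg dose) is about 8-9 h". Section 12.1 adds that "MDMA, its active metabolite MDA and the main inactive metabolites HMMA and HMA will be determined in plasma".

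**The concern.** A claim that an increase stays under 30% is a claim about an upper bound. A test whose null hypothesis is no difference does not address it. A small or noisy trial may find no significant difference when the true increase is 30%. A precise trial may find a significant difference when the true increase is 15%, well inside the bound. If the ANOVA result is taken as the answer to hypotheses 2 and 3, the trial can be wrong in either direction. How often depends on a variability that the protocol does not state.

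A second, smaller issue is scope. The expected mechanism is CYP2D6 inhibition (section 7.2.2), yet exposure is measured for less than one MDMA half-life. Section 7.2.2 speaks of AUC without limit, while section 9.2 speaks of AUC0-6h.

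**Working it through.** **No PK figure to reproduce.** The two power figures in section 13.1 reproduce with the known-SD normal formula: Φ(20√13/25 − 1.96) = Φ(0.924) = 82%, and Φ(10√8/10 − 1.96) = Φ(0.868) = 81%. Neither concerns PK.

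**Does the two-factor model fit?** Take MDMA exposure as zero in the two sessions without MDMA. Write A for placebo-MDMA and B for duloxetine-MDMA. The duloxetine main-effect contrast is (B + 0) − (A + 0) = B − A, and the interaction contrast is (B − A) − (0 − 0) = B − A. Both reduce to the same paired difference. The MDMA main effect is non-zero by construction, and Tukey adjusts for pairs that carry no PK question. The zeros also rule out a log transformation across all four sessions. The same holds for duloxetine exposure with the roles exchanged. Only a paired comparison of two sessions is informative.

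**What can a paired difference test tell us?** Inputs: n = 16 (section 10.4.1) and n = 13, the floor in section 14.4.7. Within-subject CV is assumed at 20, 25 and 30%. Log scale, two-sided α 0.05.

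- SD of the log difference = √(2 ln(1 + CV²)); SE = SD/√n; the test statistic is noncentral t with n − 1 degrees of freedom and noncentrality ln(ratio)/SE.
- Example, CV 25%, n = 16: SD = √(2 × 0.0606) = 0.348; SE = 0.0871; critical t = 2.131.
- True ratio 1.15: noncentrality 0.1398/0.0871 = 1.605, significant in 32%.
- True ratio 1.30: noncentrality 0.2624/0.0871 = 3.014, significant in 80%, so non-significant in 20%.
- Bound test at true ratio 1.10: noncentrality (0.0953 − 0.2624)/0.0871 = −1.919. The upper 90% limit falls below 1.30 when t < −1.753, which happens in 57%.

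| Assumed CV | n | Difference test significant, true ratio 1.15 | Difference test non-significant, true ratio 1.30 | Upper 90% limit below 1.30, true ratio 1.10 |
|---|---|---|---|---|
| 20% | 16 | 46% | 6% | 74% |
| 25% | 16 | 32% | 20% | 57% |
| 30% | 16 | 24% | 34% | 46% |
| 20% | 13 | 38% | 13% | 65% |
| 25% | 13 | 27% | 30% | 49% |
| 30% | 13 | 20% | 45% | 39% |

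With the bound test, the chance of wrongly supporting the hypothesis at a true ratio of 1.30 is 5% in every row.

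**What does the 0-6 h window see?** This uses a linear one-compartment model with first-order absorption and constant volume V and bioavailability F, for MDMA only. Half-life 8.5 h gives k = 0.0815/h. Solving ln(ka/k)/(ka − k) = 2.2 h gives ka = 1.36/h. In units of FD/V (D the dose), AUC0-6h = ka/(ka − k) × [(1 − e^(−6k))/k − (1 − e^(−6ka))/ka] = 4.27, and total AUC = 1/k = 12.3, so the window holds 35%. Halving clearance (k = 0.0408) gives AUC0-6h = 4.73. The ratio is 1.11, while total AUC doubles. Over half-lives of 8-9 h and tmax of 2.0-2.4 h, halved clearance raises AUC0-6h by 10-12% and Cmax by 6-9%.

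**The case against.** Section 13.2 does not expressly assign the ANOVA to the PK parameters. It treats them in separate sentences and allows further PK analyses, and an SAP that is not shown may add a ratio with an interval. That is fair, and the planned data would permit it. But the protocol itself fixes the 30% bound, and the one inferential method it names cannot test that bound. The mismatch lies in the stated text and is more than a detail left for later.

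The error rates rest on an assumed CV. That also stands. Choosing the CV to suit each error would give more striking figures: 70% significant at a true ratio of 1.15 (CV 15%, n = 16) and 45% non-significant at 1.30 (CV 30%, n = 13). These cannot both hold in one trial. With CV 15% and n = 16 the second figure is 0.4%; with CV 30% and n = 13 the first is 20%. The table therefore uses matched inputs.

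A reader might also infer that AUC0-6h is the wrong measure and that an undetected PK interaction could distort the reading of the drug effects. The protocol does not support that. The hypotheses already say AUC0-6h, section 11.4.5 chooses the window openly, and section 14.2.6 has MDMA effects gone within 5-6 h. Exposure over 0-6 h is the relevant exposure for the acute response. If slower clearance hardly moves it, slower clearance hardly confounds that response. The insensitivity is also conditional: a rise in bioavailability would show in full proportion in both measures, and section 11.5.2.2 describes autoinhibition and non-linear kinetics that the linear model leaves out.

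**Conclusion.** The point holds for hypotheses 2 and 3. A bounded claim is paired with a difference test that cannot establish or refute it, and with a factor structure that collapses to one paired comparison for each analyte. The logical fault needs no assumption. Its size does: with 16 subjects and CV 20-30%, the difference test is significant in 46% down to 24% of trials when the true ratio is 1.15, and non-significant in 6% up to 34% when it is 1.30. Two of the five secondary hypotheses are affected; the primary outcome is not.

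The window is a secondary matter of scope. Cmax and AUC0-6h suit the acute-effect question, but under the stated model they respond weakly to reduced systemic clearance of MDMA. They should not carry conclusions about total exposure or CYP2D6 inhibition on their own. No such model was run for duloxetine, so for that drug only the argument about the test applies.

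**What to change.** - **Section 13.2:** for each analyte, compare log Cmax and log AUC0-6h between the two sessions in which it was given. Report the geometric mean ratio with 90% CI, and call the hypothesis supported only if the upper limit is below 1.30.
- **Same place:** state that power is modest (n = 16, true ratio 1.10: 74/57/46% at assumed CV 20/25/30%), so failure to support is not evidence of an increase of 30% or more.
- **Section 7.2.2:** align the unrestricted AUC with the 0-6 h wording of section 9.2, and limit PK conclusions to that window.
- **Supportive measure:** report the HMMA/MDMA ratio of AUC0-6h as the indicator of CYP2D6 inhibition.

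The cost is a few sentences. HMMA is already assayed, so no new samples or assays are needed. The price is that a true hypothesis will often go unsupported.
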